#### Blinding

2.16.2.

Randomization was performed after approval for the study was obtained for a site in a new neighborhood so that the randomization assignment would not influence a site’s willingness to participate. Notably, the PI was blinded from randomization until she had successfully recruited a site to participate in the study. Due to the study design, investigators, research staff, community partners, facilitators, and youth participants could not be blinded to study assignment.

### Data collection, management, and analysis

2.17.

#### Data collection

2.17.1.

There are several points of data collection throughout the study, starting at baseline all the way through T3: baseline surveys, feedback forms, End of Program (EOP) survey, T2 and T3 follow up surveys. The surveys are all anonymous, linked by a personal study code that youth create by answering a series of questions that only they know the answer to at the beginning of each survey. This method of using a personal study code was selected to ensure anonymity and increase the likelihood of honest responses. [96–99]

In addition to survey data, other sources of data for this study (primarily for process evaluation and assessing intervention fidelity) include: 1) feedback forms completed by youth after the end of each session; 2) fidelity forms completed by research assistants at each session; 3) interviews with site leads and facilitators; 4) confidential interviews with youth (after Time 3 data collection).

#### Data management

2.17.2.

Baseline and follow-up survey participation coincided with the beginning of the intervention (Time 1), end of the program (EOP), and three (T2) and nine (T3) months following the end of the 18 h program (i.e., round). All sites conduct web-based surveys (back up paper surveys are used as needed) on tablets using REDCap, an online data management and survey system. Participation in the 3- and 9-month follow-up surveys (T2 and T3 surveys, respectively) are facilitated via tracking of participants with the help of community partners at each site. Youth provide detailed contact information at baseline to facilitate follow up. Contact information is confirmed again at sessions following the baseline survey, and at the T2 survey. Youth are also called or texted periodically by research assistants between follow-up surveys to ensure that contact information is still valid. Finally, for those that miss an EOP or T2 survey in the appropriate time frame, a comprehensive “make-up” survey is offered (with the same monetary compensation) to update contact information and increase the likelihood they’ll participate in the next survey.

Responses to the anonymous web-based secure survey are entered by the youth participants themselves on an electronic tablet; no data are stored on the computers themselves. Only research staff who have been added to the project can access this online database. Data are downloaded and stored on a password-protected share drive that can only be accessed by users with the appropriate permissions. No names are connected to the survey data as each participant creates their own secret code as described above.

The only study documents that contain unique personal identifiers are contact forms and the contact list of participants (youth and prevention educators) that are kept to assist with re-contacting participants for follow up surveys). Contact forms are stored in a secure file drawer inside the locked office of the PI whenever not in use. Contact forms are stored separately from any survey data collected in this study (the survey data are collected via computer and immediately housed in a password-protected secure database). The names of participants are kept in encrypted files on a password-protected server behind the UPMC firewall.

#### Process evaluation data collection

2.17.3.

Data are collected to assess the quality of program implementation. Research assistants are present at each intervention session and complete a fidelity form to ensure consistent implementation of the intervention or control program as intended as well as unforeseen barriers to implementation. These feedback forms are reviewed by the lead facilitators and PI regularly to provide immediate feedback to facilitators should mid-point corrections be needed.

Youth also complete a feedback form at the end of each session which is reviewed by the facilitators and research assistant to gauge youth interest and engagement in the topics and to make mid-point adjustments to program content and delivery as needed.

In addition to the end of program survey that encourages youth to provide feedback on the entire 18-h curriculum, after completion of the T3 (final) follow up survey, youth in the intervention arm are invited to participate in a semi-structured interview about their experiences with the program. Interviews with site leads and facilitators provide additional feedback on the program to guide ongoing implementation including sustainability in the participating neighborhoods. Collectively, process evaluation data will be used to inform and improve the intervention content and implementation guidance.

### Statistical methods

2.18.

Generalized linear mixed models will be used to account for the correlation among youth from the same cluster as well as the correlation between observations from the same youth. Descriptive statistics will be used to summarize the sample with regard to baseline characteristics of interest. Means and standard deviations will be presented for continuous variables, while sample proportions will be provided for categorical variables. 95% confidence intervals will accompany all sample statistics. Primary assessment of intervention effects will be based on intent-to-treat estimates. As-treated, or treatment-on-the-treated (TOT), effect parameters will be estimated in secondary analyses and reported as exploratory. Between-site differences regarding intervention effects will be assessed based on level of staff/facilitator engagement in curricular delivery as well as other observed external factors that may interact with the intervention to alter outcomes. SAS software will be used for all statistical analyses.

To assess differences at baseline between the youth in the experimental and control groups, demographics such as grade-level, race, nativity, and parental education will be compared while accounting for within-neighborhood clustering. Demographic variables as well as neighborhood-level characteristics resulting in between-arm imbalances will be considered as covariates in the primary and secondary analyses.

Participation bias will be assessed by comparison of age and race/ethnicity of youth participating in the study compared to the overall demographics of adolescents (school district and census data). Significant differences detected via chi-square analysis will be noted as potential validity threats.

An attrition analysis will be conducted by comparing youth who completed follow-up surveys with those who did not with regard to demographics as well as outcomes measured at baseline. All hypotheses will be two-sided tests with a significance level of 5%.

Missing data were minimized as much as possible by keeping the surveys as short as possible to reduce survey burden, encouraging youth to be as complete and honest as possible by ensuring anonymity of the surveys, and working assiduously with community partners to ensure that youth stay engaged and can be tracked to complete follow up surveys. Mechanisms for missing data will be investigated by comparing important covariates between youth with and without missing data at each time point. We will characterize these mechanisms as 1) missing completely at random (MCAR), 2) missing at random (MAR), or 3) not missing at random (NMAR). If the nature of our missing data is ignorable (either MCAR or MAR), our primary analysis will be sufficient given that it is a likelihood-based approach to handling missing data. Additionally, we will conduct various sensitivity analyses such as multiple imputation via chained equations (MICE) and complete-case analyses. If our missing data is non-ignorable (MCAR), we will investigate other methods such as joint or shared parameter models.

The primary outcome for this study is reductions in self-reported perpetration of SV and ARA at Time 3, compared to controls. We will examine whether Manhood 2.0 results in improvements in the primary outcome assessed at 9 months after end of program (Time 3) compared to controls. Generalized linear mixed models (GzLMM) will be used and will include variables for baseline SV/ARA perpetration, treatment group, and random effects for cluster. For the primary outcome and other binary outcomes, the GzLMMs will be fit using a logit link; for all other continuous outcomes, an identity link function will be used.

For positive bystander intervention and the remaining secondary outcomes, the models will include variables for the secondary outcome at baseline, treatment group, and random effects for cluster. This will allow us to assess the effect of the study arm after accounting for clustering within neighborhoods. As an exploratory analysis, all three time points will be included in a single generalized linear mixed model to quantify the long-term trajectories of each of the secondary outcomes.

Following Twisk and Proper’s recommendations for randomized controlled trials with both baseline and follow up measures (in this case abuse perpetration) [100], we will also construct multinomial logistic regression models that account for presence or absence of baseline perpetration. That is, we will examine intervention effects among youth reporting baseline SV/ARA perpetration and the likelihood of becoming ‘non abusive’ at follow up (i.e., an ‘early intervention’ effect). Similarly, we will examine intervention effects among youth with no baseline SV/ARA perpetration and the likelihood of ‘staying non abusive’ (i.e., a primary prevention effect). We have used this approach to analyze intervention effects on abuse exposure in our school health center relationship abuse prevention study [101].

We will also conduct two sets of exploratory analyses. First, we will conduct an intensity-adjusted analysis that reflects the actual delivery of the program. To achieve this, we will use a continuous score of “intensity” to replace the binary intervention variable in the models for the primary analysis. This score will be calculated for each round (program delivery) by using two sources of information. The first is information collected systematically about each session by trained research assistants who observed the sessions, including whether each task assigned to a module was performed (yes or no). The second is a summary measure of overall attendance for each round, tracked by using sign-in sheets with the research assistants. The second set will be a per-protocol analysis. This set of models will include only participants in the intervention arm that received the full intervention, defined as having covered a minimum threshold of tasks across the six sessions and having sufficient attendance. These measures replicate the intensity score values, but are then dichotomized to yes or no to receiving the full intervention. All control arm participants will be included in these models.

To explore whether demographics, youth pre-intervention risk and protective factors (e.g., history of SV/ARA exposure, sexual risk, connectedness), and site-level differences (e.g., staff experience, organizational capacity, intervention intensity) moderate the effect of the intervention on the primary and secondary outcomes, linear mixed models slightly different from those described above will be utilized. The outcome variables will be modeled as a function of the following variables: the outcome at baseline, the treatment group, the potential moderator, the interaction between the treatment group and moderator, and a random effect for cluster. A significant interaction suggests the presence of intervention effect heterogeneity, and we will follow the approach of Kraemer [102] by focusing on effect size derivation rather than formal hypothesis testing.

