#### Study setting and site eligibility criteria

2.4.1.

This study involves 20 neighborhoods and 21 clusters in the Pittsburgh area; within each neighborhood, one to four different community partner organizations (referred to as “community partners” here) participated. Neighborhoods were recruited by identifying a potential community partner who could host the program and were willing to be randomized to receive the intervention or control programming. These community partners included youth-serving organizations, YMCA, Urban League, faith-based organizations, and libraries. Additionally, we partnered with the county’s community intensive surveillance program, a diversion program for youth involved in the juvenile justice system.

Neighborhoods were identified based on having sites where the YMCA, Urban League, or other youth serving partners had existing programs and which were considered lower income communities based on census information and school district data. Asset maps were created for each neighborhood with the goal of identifying community champions and youth-relevant resources to support this community-based project. The strong partnerships established with key stakeholders in each of these sites (including site coordinators, facilitators, and community members) facilitated recruitment and retention as described below.

Among the 20 participating neighborhoods, the proportion of students attending public high schools in those neighborhoods considered economically disadvantaged ranges from 32 to 100%; the high school graduation rate for those same school districts ranged from 63 to 97%. Each of these neighborhoods struggle with poverty, school ‘push-out’ (disciplinary actions that push youth, especially African American boys, out of the regular school system), and among the highest rates of gang and gun violence in the county (see Table 1 for neighborhood characteristics). These characteristics were compared by treatment arm using Kolmogorov-Smirnov two-sample exact tests due to their nonnormal distributions. Neighborhood characteristics did not vary between the intervention and control arm neighborhoods.

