## Results

3.

Related to recruitment, at least one site from the 21 neighborhoods agreed to participate (Fig. 3). Eleven neighborhoods were allocated to the experimental condition and ten to the control condition, and the neighborhood characteristics were similar between intervention and control neighborhoods (Table 3). There were a total of 866 age-eligible male youth who attended the program (464 in the experimental group; 402 in the control); all 866 enrolled in the study and completed a baseline survey (100% participation).

As detailed in Table 3, most participants (70%) identify themselves as Black or African American and 88% were born in the US. Participants’ age ranges overall were roughly evenly divided across 13–14, 15–16, and 17–19; the intervention arm had a slightly lower proportion of 13–14 year olds and higher proportion of 15–16 year olds compared to the control arm. At the time of their baseline survey, 22% were in middle school and 62% were in high school.

Compared to the control arm, the intervention group had higher proportions of those who self-identified as White, Multiracial, or Other racial category, and lower proportions of those who self-identified as Black/African American or Hispanic. Intervention and control arm participants were similar in all other characteristics.

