**Fig. 3. F3:**
[figure not shown]
CONSORT diagram.

**Table 1: T1:** Neighborhood characteristics.

Neighborhood	Non-white students	Economically Disadvantaged^a^	Student stability rate^b^	Graduation rate^c^	Chronic Absenteeism^d^	School Suspension^e^
Control (median)	84%	80%	81%	81%	56%	30%
Allentown/Beltzhoover/Hilltop*	45%	66%	83%	86%	43%	23%
Clairton^†^	81%	99%	n.a.	79%	n.a.	n.a.
Garfield*	95%	81%	81%	81%	56%	31%
Hazelwood*	52%	40%	88%	88%	28%	12%
Hill District*	95%	81%	81%	81%	56%	31%
North Braddock^†^	65%	100%	n.a.	83%	n.a.	n.a.
Northside*	87%	79%	70%	72%	69%	30%
Northview*	87%	79%	70%	72%	69%	30%
Downtown*	64%	67%	88%	92%	13%	23%
Wilkinsburg*	99%	80%	72%	77%	66%	36%
**Intervention (median)**	**52%**	**64%**	**72%**	**84%**	**66%**	**36%**
Duquesne^†^	35%	45%	n.a.	93%	n.a.	n.a.
East Hills*	52%	40%	88%	88%	28%	12%
East Liberty*	99%	80%	72%	77%	66%	36%
Homewood*	99%	80%	72%	77%	66%	36%
Larimer*	99%	80%	72%	77%	66%	36%
McKeesport^†^	51%	100%	n.a.	85%	n.a.	n.a.
Munhall^†^	38%	56%	n.a.	97%	n.a.	n.a.
Penn Hills^†^	67%	61%	n.a.	84%	n.a.	n.a.
Prospect Park^†`^	16%	33%	n.a.	94%	n.a.	n.a.
Sheraden*	64%	64%	85%	78%	36%	17%
Wilmerding^†^	41%	100%	n.a.	79%	n.a.	n.a.
Kolmogorov-Smirnov two-sample exact test comparing intervention and control, *p*-value	0.3230	0.1088	0.8695	0.5783	0.8695	0.2945

n.a. indicates data were not available for the neighborhood school district.

* Reference [103].

† Reference [104].

a Economically disadvantaged: Students are identified as economically disadvantaged based on the state’s Direct Certification process, which can include poverty data sources such as the Supplemental Nutrition Assistance Program, Transitional Assistance for Families with Dependent Children, or Medicaid eligibility; and children living in foster care.

b Student stability rate: total number of students who didn’t transfer during the entire year divided by the official enrollment for that year, which is calculated in October.

c Graduation rate: rate of individual 9th graders in 2012 who graduated in 2016 or earlier.

d Chronic absenteeism: the percentage of students who were absent 10% or more of the days they were enrolled in the school.

e School suspension: percentage of students who were suspended (out-of-school suspensions only) at least once during the school year.

**Table 2 T2:** Individual youth-level outcome measures.

Construct	Response options	Surveys				Items

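### Beyond the baseline outcome, covariates for the primary model are chosen by observed imbalance with no criterion, the randomisation stratum is not listed, and non-significant tests on 21 clusters are read as balance

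*Protocol article*

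**What the plan says.** Section 2.18 (Statistical methods) gives the generalised linear mixed model for the primary outcome, which "will include variables for baseline SV/ARA perpetration, treatment group, and random effects for cluster". Any other adjuster falls under a separate rule in the same section: "Demographic variables as well as neighborhood-level characteristics resulting in between-arm imbalances will be considered as covariates in the primary and secondary analyses". The rule names no test, threshold or list.

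Section 2.16.1 (Randomization) says that the first 10 clusters were stratified by lead site (YMCA, Urban League or Other) and the next 11 by type of site. That factor does not appear among the model terms in section 2.18.

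On neighbourhood balance, section 2.4.1 reports: "These characteristics were compared by treatment arm using Kolmogorov-Smirnov two-sample exact tests due to their nonnormal distributions". It concludes: "Neighborhood characteristics did not vary between the intervention and control arm neighborhoods". The Results section repeats that "the neighborhood characteristics were similar between intervention and control neighborhoods". Table 1 prints the arm medians and six exact p-values: 0.3230, 0.1088, 0.8695, 0.5783, 0.8695 and 0.2945.

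**The concern.** There are two linked faults.

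**The selection principle.** Adjustment helps when a covariate predicts the outcome. Whether it happens to differ between arms is a poor guide to that. A rule triggered by imbalance can pass over a strong predictor that looks balanced and admit a weak one that does not. With no criterion, two analysts could reach different primary models from the same data. A factor used to stratify randomisation would normally be in the model whatever the balance.

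**The reading of the tests.** With 10 v 11 clusters, and 8 v 5 for three of the six measures, a non-significant Kolmogorov-Smirnov test says little about whether the arms are alike. If the section 2.4.1 conclusion is carried into the section 2.18 rule, no neighbourhood variable qualifies for consideration, although Table 1 shows sizeable differences.

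At stake are the reproducibility of the primary model, some precision, and a possible shift in the estimated arm difference if the unbalanced neighbourhood characteristics are prognostic.

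**Working it through.** **Inputs.** Cluster values by arm from Table 1 (10 control, 11 intervention; 8 v 5 for stability, absenteeism and suspension, because of n.a. entries). ICC 0.01, 20% rate and target difference 8.3 points from section 2.12.

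**1. Reproducing the article's figures.** Full enumeration of the permutation distribution, conditional on ties, returns all six p-values to four decimals. The medians also reproduce: non-white 84.0 v 52.0; economically disadvantaged 79.5 (printed as 80) v 64.0.

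**2. Size of the differences.** Standardised difference = mean gap / √[(SD₁² + SD₂²)/2].

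| Measure | Control mean (SD) | Intervention mean (SD) | Gap | Standardised | KS p |
|---|---|---|---|---|---|
| Non-white, % | 77.0 (19.2) | 60.1 (28.6) | 16.9 | 16.9/24.4 = 0.69 | 0.323 |
| Economically disadvantaged, % | 77.2 (17.2) | 67.2 (22.8) | 10.0 | 10.0/20.2 = 0.50 | 0.109 |

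The 32-point non-white figure is a gap in medians; the gap in means is about half of it.

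**3. What the test could detect.** Simulated power of the exact test, normal data, two-sided 5%:

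| True shift | 10 v 11 | 8 v 5 |
|---|---|---|
| 0.5 SD | 15% | 11% |
| 0.8 SD | 30% | 19% |
| 1.0 SD | 44% | 29% |
| 1.5 SD | 81% | 53% |

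For a true shift equal to the non-white mean gap (16.9 points, pooled SD 24.6) power is about 25%. For a true 32-point shift it is about 67%.

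**4. Possible effect on the unadjusted arm difference.** Between-cluster SD of the outcome = √(0.01 × 0.20 × 0.80) = 0.040, or 4.0 points. The non-white gap in units of the SD over all 21 clusters is 0.66. If the characteristic explains a share R² of the between-cluster variance, the shift is 4.0 × √R² × 0.66 points. The article gives no R², so this is a range over an assumption:

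| R² | Shift (points) |
|---|---|
| 0.10 | 0.8 |
| 0.25 | 1.3 |
| 0.50 | 1.9 |
| 1.00 | 2.7 |

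The target difference is 8.3 points. The direction of any shift cannot be determined from the article.

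**The case against.** The strongest reply is that section 2.18 ties imbalance to no test, that the Kolmogorov-Smirnov comparisons are descriptive, and that a final adjuster list is commonly left to an analysis plan that is not shown. The first two points stand. The third stands only for the detail of the list: the article states a selection principle for the primary analysis, and the principle itself is the weak part.

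Several stronger readings are tempting but not supported:

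- *All covariates are conditional on imbalance.* They are not; baseline perpetration is always in the model.
- *The neighbourhood gap will be left unadjusted.* The article nowhere says so. Under the rule as written, the gap, or participant race (p = 0.0075 in Table 3), could still be taken up.
- *The tests could not have seen a 32-point difference.* Power for a true shift of that size is about 67%. It is low for the mean gap.
- *Participants differ by 32 points.* Table 1 holds school-level figures, several rows are identical (15 of 21 are distinct), and enrolled youth differ by 4.8 points on Black/African American identity (72.9% v 68.1%).
- *The rule would drop clusters by admitting variables with n.a. entries.* Those three have p-values of 0.2945 to 0.8695. If non-significance keeps variables out, these would not enter.
- *The race difference shows selection after allocation.* The article does say that "research staff, community partners, facilitators, and youth participants could not be blinded to study assignment", which makes selection possible, but nothing shows that it produced the difference.

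It is also fair that the random cluster effect already allows for chance differences between clusters in the standard error. It does not remove the shift in the estimate from the particular imbalance observed.

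**Conclusion.** The point holds in a limited form. Section 2.18 lets the primary model depend on observed imbalance, without a criterion and without the randomisation stratum among its terms. Section 2.4.1 treats non-significance on 21 clusters as absence of difference, although the table it summarises shows standardised differences of about 0.69 and 0.50 on two poverty- and composition-related measures. Taken together, the article's own conclusion leaves its rule with no reason to adjust for them; that is an inference from reading the sections together.

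The likely numerical consequence is modest: about 0.8 to 1.9 points if percent non-white explains 10% to 50% of between-cluster variance, and 2.7 points at the extreme, against a target of 8.3. This rests on the planning ICC and rate and on an assumed R². The power figures assume normal data, whereas the article describes the characteristics as nonnormal, so they are approximate. Nothing here shows that the trial's result will be biased.

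**What to change.** Before T3 outcomes are compared by arm, replace the imbalance rule with a list fixed without regard to observed balance:

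- baseline outcome (already in the model);
- randomisation stratum (lead site / type of site);
- age group;
- race/ethnicity;
- at most one neighbourhood variable available for all 21 clusters, either percent economically disadvantaged or percent non-white. Stability, absenteeism and suspension are n.a. for 8 clusters, 6 of them intervention, and are unsuitable.

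Report the model with baseline perpetration, arm and cluster effect only as a sensitivity analysis. In section 2.4.1 and the Results, replace the statement that neighbourhoods were alike with a description of the observed differences; the medians are already in Table 1.

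**Cost.** About three of the 19 between-cluster degrees of freedom (21 clusters less 2 arms): two for the stratum, assuming three levels throughout, and one for the neighbourhood variable. The odds ratio from the logit model becomes conditional on the added covariates, which the report should state. Race counts in Table 3 sum to 816 of 866 (609 + 29 + 53 + 55 + 70), so the list must also say how the 50 participants without a recorded race are kept in the analysis. Otherwise the change is to wording only.

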#### SV/ARA perpetration

2.10.1.

At baseline and T3 (9 months post-intervention), participants report whether they perpetrated the following SV or ARA behaviors in the last 9 months. The primary outcome measure for the study is any report of SV or ARA perpetration, i.e., yes to any of the following items.

The following two constructs focus on ARA behaviors against a dating partner. “Any ARA perpetration” is measured as a yes to any of these 13 items.

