The study also has several limitations. The surveys are collected anonymously with each participant creating their own personal identification code that only they will know to match surveys over time. Thus, the dosage of program received (i.e., proportion of program completed) can only be calculated at the level of each round rather than at the individual level. As a community-based study recruiting youth who are at high risk for school ‘push out,’ retention of this cohort remains a critical challenge, with the most vulnerable at especially high risk for being lost to follow up. Additionally, youth who are juvenile justice system-involved are particularly difficult to retain. Thus, we are likely to have significant missing data from rounds involving justice system-involved youth. We will conduct sensitivity analyses both with and without these youth in the sample to examine differences in intervention effects.

In summary, this study protocol is intended to evaluate Manhood 2.0 using a rigorous design to determine the effectiveness of a community-based sexual violence and adolescent relationship abuse prevention program for high school age youth living in low resource neighborhoods. Findings may provide urgently needed information about the effectiveness of a gender transformative program that combines healthy sexuality skills, gender norms change, and bystander skills to interrupt peers’ disrespectful and harmful behaviors to reduce SV/ARA perpetration among adolescent males.

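### The missing-data plan calls the T3-only primary model sufficient under any MAR; it is valid only under MAR given the model's own terms, and the switch to NMAR methods cannot be decided from observed data

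*Protocol article*

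**What the plan says.** All references are to the protocol article.

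- **When the outcome is measured.** Section 2.10.1: "At baseline and T3 (9 months post-intervention), participants report whether they perpetrated the following SV or ARA behaviors in the last 9 months". Table 2 shows the same: no perpetration item is asked at end of program or T2.
- **The primary model.** Section 2.18: "Generalized linear mixed models (GzLMM) will be used and will include variables for baseline SV/ARA perpetration, treatment group, and random effects for cluster". The link is logit. The section opens by mentioning correlation between observations on the same youth, but the primary model has no such term and no second follow-up observation to which it could apply.
- **The missing-data argument.** If missingness is MCAR or MAR, "our primary analysis will be sufficient given that it is a likelihood-based approach to handling missing data". MICE and complete-case analyses are named as sensitivity analyses.
- **How the mechanism is decided.** By comparing covariates between youth with and without missing data at each time point. Then: "If our missing data is non-ignorable (MCAR), we will investigate other methods such as joint or shared parameter models".
- **Expected loss.** Section 2.12 plans 80% retention at T3. The Discussion describes retention as a critical challenge, "with the most vulnerable at especially high risk for being lost to follow up", expects substantial missing data from rounds with justice-involved youth, and plans analyses with and without them.

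**The concern.** A likelihood analysis is protected under MAR only with respect to the data that enter the likelihood. In a longitudinal model, intermediate outcomes on youth who later drop out do enter it. Here they do not, because the primary outcome has no intermediate measurement and T2 data are not in the model. The statement of sufficiency under MAR in general is therefore broader than the model supports.

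Two consequences follow. A complete-case check on the primary outcome offers no contrast with the primary result. And the methods for non-ignorable missingness are held back until a classification that observed data cannot supply. At stake is whether a reader can judge how far the primary result depends on the youth whom the authors themselves expect to lose.

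**Working it through.** **1. Size of the problem, from the plan's figures.** Section 2.12 gives 866 youth and 80% retention: 866 × 0.8 = 692.8 with T3, and 866 × 0.2 = 173.2 without. The planned difference is 8.3 points on a 20% control rate (8.3 / 20 = 41.5%, the stated 42%).

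**2. What a youth without T3 contributes.** Given the cluster effect u, a youth with T3 contributes P(y | baseline, arm, u). A youth without T3 contributes the sum over y = 0, 1 of the same quantity, which is 1. Multiplying by 1 inside the cluster integral changes nothing. A numerical check on one simulated data set (21 clusters of 41, 861 youth, 679 with T3) agreed. With non-responders integrated out, and with them dropped, the arm log odds ratio was −0.6776 and the log-likelihood −302.3228 both times. The primary fit is the T3-responder fit.

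**3. When that fit is valid.** Large-sample logistic fits of T3 perpetration on baseline perpetration and arm were made with 20% missing overall. The cluster effect was omitted and the missingness mechanisms were assumed. The variable outside the model had a log-odds effect of 1.0 (moderate) or 2.0 (strong) on T3 perpetration. Where two values stand after the arrow, dropout depended on that variable less and then more strongly.

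| Missingness depends on | Moderate predictor: full-data OR → responder OR | Strong predictor: full-data OR → responder OR |
|---|---|---|
| Arm and baseline perpetration (in the model) | 0.507 → 0.506 | 0.513 → 0.510 |
| Outside variable, same in both arms | 0.507 → 0.506 | 0.513 → 0.510 |
| Outside variable, intervention arm only | 0.507 → 0.462, 0.427 | 0.513 → 0.424, 0.357 |
| Same, no true effect | 1.000 → 0.914, 0.848 | 1.000 → 0.833, 0.709 |

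The third and fourth rows are MAR, since the outside variable is observed, and the model does not handle them. The first two rows show no material bias in the odds ratio.

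**4. The complete-case analysis.** The Results section reports that all 866 youth completed a baseline survey, and a mixed model drops records with missing covariates in any case. For the primary outcome, complete cases in the usual sense are the T3 responders of step 2.

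**5. The NMAR trigger.** MAR and NMAR differ in whether missingness depends on the unobserved T3 outcome once observed data are accounted for. Comparing observed covariates by missingness status can give evidence against MCAR but says nothing about that dependence. The text also puts MCAR on the ignorable side and then attaches the same label to the non-ignorable case.

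**6. What non-ignorable loss could do.** With 20% loss in both arms, full-sample difference = 0.8 × observed difference + 0.2 × difference among the lost.
- Lost youth show no effect: 0.8 × 8.3 + 0.2 × 0 = 6.6 points.
- Lost youth differ by 10 points the other way: 6.64 − 2.0 = 4.6 points.
- To cancel the observed 8.3 points entirely, the lost would need a reverse difference of 6.64 / 0.2 = 33.2 points.

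The effects among lost youth are assumed; nothing in the article estimates them.

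**The case against.** The strongest reply is that being restricted to responders does not in itself make the sufficiency statement wrong. When only the outcome is missing, the responder likelihood is the full observed-data likelihood, and it is valid under MAR given the model's terms. This stands. A reader might infer that the likelihood argument fails simply because the model is complete-case; the first two rows of the table show that it does not. Material bias in the odds ratio under MAR needed dropout that acted differently by arm on a variable outside the model. The Discussion predicts high loss among vulnerable youth, not loss that differs by arm. Arm-specific loss cannot be excluded, however, since section 2.16.2 says participants and staff are unblinded.

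A reader might also infer that the primary result has no protection. The article does not support that. MICE is planned, analyses with and without justice-involved youth are planned, section 2.18 includes an attrition analysis, and variables imbalanced between arms will be considered as covariates (race, for example, differs in Table 3, p = 0.0075). These have limits: covariates chosen for imbalance are not chosen because they predict dropout, and removing justice-involved youth changes the population analysed without recovering outcomes.

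Complete-case could mean completers of every wave or every item, and for the exploratory model of secondary outcomes ("As an exploratory analysis, all three time points will be included in a single generalized linear mixed model") it would be a different analysis. The text gives no such definition, so the redundancy is claimed only for the primary outcome in the usual sense. The wrong label is evidently a slip, but it sits in the sentence that sets the trigger. The list of imputation variables may properly be in the analysis plan, and its absence here is not a fault.

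**Conclusion.** The concern holds in limited form. The sufficiency statement should read as MAR given baseline perpetration, arm, cluster and any added covariates. The complete-case check is redundant for the primary outcome, and the NMAR trigger is unworkable and mislabelled.

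No bias is demonstrated. The odds ratios in the table rest on assumed mechanisms and on fits without the cluster effect; they show direction and range only. A reader might take the shifts from 8.3 to 6.6 or 4.6 points as the bias of the primary model. They are illustrations under chosen effects among lost youth with equal 20% loss by arm, and imputation under MAR would not correct them. They show why an NMAR analysis should always be reported.

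Nor do the documents require multiple imputation as the main analysis or promotion of the joint model for secondary outcomes. Both are options. A joint model with T2 would recover little for the primary outcome, which is not measured then.

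**What to change.** 1. Restrict the sufficiency statement in section 2.18 to MAR given baseline perpetration, arm, cluster and any covariates added to the model.
2. Make the planned MICE the required MAR sensitivity analysis for the primary outcome, replacing the complete-case analysis for that outcome. Include arm, cluster and collected variables that predict dropout: age, race, site type including justice-programme site, baseline SV/ARA items and T2 measures. The T2 measures are indirect, and they are usable only where the self-created codes link the surveys.
3. Run an arm-specific delta (tipping-point) analysis unconditionally, and report the departures from MAR at which the conclusion changes. Keep the covariate comparisons as description, not as a switch between methods.
4. Correct the label of the non-ignorable case from MCAR to NMAR.

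The cost is a few sentences and modest programming. No new data are needed, and the primary model can stay as planned.
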